## Abstract

**Background:**

Annual prevalence of gestational diabetes mellitus (GDM) is 12.5% among Finnish pregnant women. The prevalence is expected to rise with the increasing overweight among women before pregnancy. Physical activity and diet are both known to have favourable effects on insulin resistance and possibly on the risk of GDM. We aimed to investigate, whether GDM can be prevented by counseling on diet, physical activity and gestational weight gain during pregnancy.

**Methods/Design:**

A cluster-randomized controlled trial was conducted in 14 municipalities in the southern part of Finland. Pairwise randomization was performed in order to take into account socioeconomic differences. Recruited women were at 8-12 weeks' gestation and fulfilled at least one of the following criteria: body mass index ≥ 25 kg/m^2^, history of earlier gestational glucose intolerance or macrosomic newborn (> 4500 g), age ≥ 40 years, first or second degree relative with history of type 1 or 2 diabetes. Main exclusion criterion was pathological oral glucose tolerance test (OGTT) at 8-12 weeks' gestation. The trial included one counseling session on physical activity at 8-12 weeks' gestation and one for diet at 16-18 weeks' gestation, and three to four booster sessions during other routine visits. In the control clinics women received usual care. Information on height, weight gain and other gestational factors was obtained from maternity cards. Physical activity, dietary intake and quality of life were followed by questionnaires during pregnancy and at 1-year postpartum. Blood samples for lipid status, hormones, insulin and OGTT were taken at 8-12 and 26-28 weeks' gestation and 1 year postpartum. Workability and return to work were elicited by a questionnaire at 1- year postpartum. Linkage to the national birth register of years 2007-2009 will provide information on perinatal complications and GDM incidence among the non-participants of the study. Cost-effectiveness evaluation will be based on quality-adjusted life years. This study has received ethical approval from the Ethical board of Pirkanmaa Hospital District.

**Discussion:**

The study will provide information on the effectiveness and cost-effectiveness of gestational physical activity and dietary counseling on prevention of GDM in a risk group of women. Also information on the prevalence of GDM and postpartum metabolic syndrome will be gained. Results on maintaining the possible health behaviour changes are important in order to prevent chronic diseases such as cardiovascular disease and diabetes.

**Trial registration:**

The trial is registered ISRCTN 33885819

## Background

Gestational diabetes mellitus (GDM) is defined as a type of diabetes firstly diagnosed during pregnancy [1,2]. Insulin sensitivity usually decreases towards the end of pregnancy and is therefore partly physiological, but among part of pregnant women it results to glucose intolerance and GDM [3]. Prevalence estimates vary, usually approximately 5% of pregnant women develop GDM [4]. In Finland the average prevalence of GDM is 12.5%, but varies from 6 to 25% between different hospital districts, at least partly due to different diagnostic criteria [5].

Although glucose metabolism usually normalises after delivery, majority of women with GDM have an increased risk of later diabetes mellitus or impaired glucose tolerance and possibly also of metabolic syndrome [6-9]. In a Danish sample (N = 481), the prevalence of metabolic syndrome approximately 10 years after pregnancy was three times as high in women with prior diet-treated GDM as in 1000 age-matched population-based control subjects [10]. Although the prevalence of metabolic syndrome after one year is lower than ten years after delivery, women with GDM risk have been reported as forerunners of maternal and childhood obesity [8]. GDM and overall obesity among women reflects also to children's weight development. Women with GDM have more often macrosomic newborns (birth weight ≥ 4000 g) and the related health problems than other women [11]. Intrauterine hyperglycaemia may contribute to the pathogenesis of offspring overweight and metabolic syndrome later in life [12].

The most important risk factors of GDM are high maternal age, family history of type 2 diabetes and overweight before pregnancy [13] and GDM or glucose intolerance in previous pregnancies [7]. There is also some evidence that excessive gestational weight gain, high intake of saturated fat and low intake of polyunsaturated fat may increase the risk of GDM [4,14-17]. On the other hand, physical activity improves glucose tolerance and insulin sensitivity in pregnant women [18]. Physical activity before or during pregnancy is also associated with reduced risk of GDM [19-21]. In the case-control study by Dempsey et al. [22] women, who were engaged in physical activity had almost 50% reduction in risk of GDM compared with inactive women.

Lifestyle modifications have been shown valuable adjunctive therapy in the treatment of GDM [23]. Moreover, there is encouraging evidence on the impact of lifestyle interventions to prevent the progression of GDM to type 2 diabetes in women with history of GDM [24]. The small trials by Mottola et al. [25] and Hui et al [26] showed promising results in preventing GDM with nutrition and physical activity modification. In our own pilot study (n = 105), pregnant women who had intensified dietary and physical activity counseling at routine maternity clinic visits were able to change their diet to favourable direction and to maintain at least moderate physical activity more often than the women with routine counseling [27,28]. Interestingly, there were no high birth weight newborns in the intervention group, but eight of them (15%) in the control group, suggesting that the intervention may have had beneficial effect on maternal glucose tolerance.

The evidence for the effect of lifestyle modification in preventing GDM will accumulate in the future from ongoing studies by Chasan-Taber et al [29] and Oostdam et al [30] and from our study presented here. The *primary objective *of our trial is to show whether individual counseling on physical activity, diet and gestational weight gain can have preventive effect on the development of GDM. *Secondary objectives of our trial *are to evaluate maternal and child weight development, maternal metabolic changes, and changes in maternal physical activity and dietary habits and quality of life. Cost-effectiveness of the trial is evaluated since the prevention of GDM is important in order to reduce direct health care costs, such as hospital days and surgical procedures and indirect costs due to sick leave during pregnancy. To date no cost-effectiveness studies have been published on the prevention of GDM. The purpose of this paper is to describe the design and the methods of a cluster-randomized controlled trial (RCT) to prevent GDM and its 1-year follow-up.

## Methods/Design

### Study design, setting and group allocation

The RCT was conducted in primary health care maternity clinics in Pirkanmaa region, situated south-western part of Finland (Figure 1). The prevalence of GDM was 17% in Pirkanmaa region in 2004[5]. Municipalities in Pirkanmaa region with at least 70 annual deliveries were contacted and recruited to the study (N = 14). The city of Tampere, with more than 200.000 inhabitants and 23 maternity clinics, was the biggest of these municipalities. However, it was the only municipality restricting the number of participating maternity clinics to one due to the extra workload accumulated to the nurses from the study arrangements and counseling. All clinics from the other municipalities took part in the study.

**Figure 1 F1:**
[figure not shown]
**The trial and the control municipalities in Pirkanmaa area in south-western Finland**.

For the cluster randomisation, the municipalities were arranged into matched pairs and within each pair they were randomized to an trial and a control municipality. The pair-matching was done with regard to number of births, size and socio-economic level of the population, estimated incidence of GDM and whether the clinic situated in rural or urban area. Municipalities were randomized rather than individual clinics, nurses or pregnant women to avoid contamination.

In Finland, maternity health care is provided by the municipalities and funded through public taxation. The visits are free of charge for women. Almost all pregnant women (99.7%) utilize municipal maternity care services, although there are private services available as well [5,31]. Currently, first-time pregnant women are recommended to visit a nurse 11-15 times and a physician three times during pregnancy [31,32]. The recommended number of visits is lower (7-11) during subsequent pregnancies. The first visit to maternity clinics usually takes place when women are at approximately 8 to 12 weeks' gestation. The spouses are encouraged to attend all visits.

### Recruitment of study population

In total, 23 nurses from the trial clinics and 30 nurses from the control clinics participated in the implementation of the study. The nurses recruited pregnant women when they contacted the maternity clinic for the first time by telephone (up to 12 weeks' gestation). The women who were interested in participating in trial received an invitation letter and the informed consent form by mail. The eligible women willing to participate signed the informed consent during the first maternity visit. If the women were not eligible or not willing to participate, they were asked to complete a baseline questionnaire and another informed consent for later linkage to the birth registry information.

The nurses used structured form to keep record on the women invited and eligible to the study and of those eligible or not wanting to participate. The form also included space for entering the reasons for dropping out. Recruitment was planned to continue until at least 30 women were enrolled in each municipality. All participants of the trial including the non-participants who were willing to fill the baseline questionnaire, were included in the follow-up study. Ethical approval for this study was obtained from the Ethical board of Pirkanmaa Hospital District (Reference number R06230, 19.1.2007).

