### Intervention

The trial will continue from the first maternity clinic visit (at 8-12 weeks' gestation) until 37 weeks' gestation (Figure 2). The recommendations for gestational weight gain are discussed and the primary physical activity counseling takes place at the first visit. The primary dietary counseling session is implemented during the visit at 16-18 weeks' gestation. Both physical activity and dietary counseling are boostered at subsequent visits; physical activity at four and diet at three visits (Figure 2).

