**Figure 3 F3:**
[figure not shown]
**Design and timetable of the study: cluster-randomized controlled trial (RCT), 1-year follow-up and linkage to the medical birth registry**.

*The primary maternal outcome *of the trial is the proportion of women diagnosed with GDM, as assessed by oral glucose tolerance test during 26-28 week's gestation and the weight of the newborn adjusted for gestational age.

*Secondary outcomes *of the trial are gestational weight gain and need of insulin treatment during pregnancy determined at time of possible GDM diagnosis (earliest 26-28th week of pregnancy based on OGTT). Additional outcomes are changes in maternal physical activity (frequency and duration of total and domain-specific leisure time physical activity) and dietary habits (food choices related to the objectives of counselling, fibre intake (g/day) and proportions of saturated, polyunsaturated and total fat of total energy intake), maternal quality of life (profile of 15 health-related dimensions during pregnancy). Direct and indirect costs during pregnancy and the cost-effectiveness of the trial (based on QALYs) are calculated. Changes related to blood lipids (cholesterol, HDL-cholesterol, triglycerides, LDL-cholesterol, oxidized lipoproteins) and other biological markers of fat metabolics (IGF, IGFBp-3, C-peptide, leptin, adiponectin, para-oxonase) are determined both during pregnancy and one-year postpartum.

*The outcomes of the 1-year follow-up study *are maintenance of possible changes in physical activity and dietary habits, incidence of metabolic syndrome based on the International Diabetes Federation criteria [52], perceived workability, quality of life (RAND-36 scale), depression (Beck scale) and proportion of women returning to work after maternity leave.

*Medical birth registry linkage *includes information on perinatal outcomes (complications during pregnancy or delivery, such as pre-eclampsia, cesarean section rate and need for labour induction) and incidence of GDM among non-participants.

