#### Laboratory tests

Blood sample analyses included determination of lipids (cholesterol, HDL-cholesterol, triglycerides, LDL-cholesterol, oxidized lipoproteins) and other biological markers (IGF, IGFBp-3, C-peptide, leptin, adiponectin, para-oxonase, insulin) (Table 1). Medical laboratory technologists from the UKK Institute or from the Centre for Laboratory Medicine in Pirkanmaa hospital district took the blood samples (4 × 10 ml) and performed the OGTT for all participating pregnant women. Specimens are analyzed in analysed at [name]'s laboratory at Georgetown University, Washington DC, USA (IGF-1, IGFBP-3, estradiol, progesterone, C-peptide) and in MCA research laboratory, Turku (leptin, adiponectin, insulin, lipids) and at UKK Institute.

OGTT. OGTT was taken at 8-12 and 26-28 weeks' gestation and 1 year postpartum. Analyses were performed at UKK Institute. OGTT has been shown to be the optimal test for insulin sensitivity during pregnancy [61]. In Finnish health care OGTT is performed for women at risk of GDM 26-28 weeks' gestation, because of the expected benefits of prevention of adverse pregnancy outcome related to GDM. We followed the same timing and conveyed OGTT results to nurses who were in charge for possible further treatment. The standard OGTT was performed by giving Glukodyn^R^, including 75 g glucose in 330 ml water after overnight fasting (8 to 14 hours). The Finnish GDM criteria were used to identify participants with GDM [62,63]. Incremental and total area under curve (AUC) was also calculated based on the blood glucose values at 0, 1 and 2 hours after glucose ingestion. AUC can be used as a measure of glucose exposure and it gives a measure of how much and for how long glucose stays in the blood. A long, low concentration exposure may be as important as shorter but higher concentration. Total AUC is a descriptive factor related to basal blood glucose value, whereas incremental AUC more accurately describe glycemic response to foods [64].

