### Statistical analysis

The main method in the comparison of the trial and the control group is the multilevel analysis. In the multilevel analysis, both individual-level, nurse-level and clinic-level influences on the outcomes can be examined simultaneously and the results are corrected for between-clinic and between-nurse variation. Also non-parametric methods will be utilized when applicable. The choice of method depends on the measurement scale and distribution of the outcome variable. Intention-to-treat principle is followed, i.e. the analysis is performed in originally randomized groups. Information on drop-outs is received through linkage to birth registry. Intention-to-treat analyses are performed after birth registry linkage. A secondary analysis is performed without the drop-outs.

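### Clinic nurses recruit women after their municipality is allocated, so GDM risk can differ by arm, and the main model leaves adjustment for individual baseline risk optional

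*Protocol article*

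**What the plan says.** **Allocation.** Under Study design, setting and group allocation, "the municipalities were arranged into matched pairs and within each pair they were randomized to an trial and a control municipality". The matching factors describe municipalities: births, population size, socio-economic level, estimated GDM incidence, and rural or urban location.

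**Recruitment.** Under Recruitment of study population, "23 nurses from the trial clinics and 30 nurses from the control clinics participated in the implementation of the study", and "The nurses recruited pregnant women when they contacted the maternity clinic for the first time by telephone (up to 12 weeks' gestation". Then "The eligible women willing to participate signed the informed consent during the first maternity visit". Under Intervention, for the trial clinics, "the primary physical activity counseling takes place at the first visit". No masked recruiter, and none independent of the clinic, is described.

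**Analysis.** Under Statistical analysis, "The main method in the comparison of the trial and the control group is the multilevel analysis". The section says that individual, nurse and clinic influences are open to examination in this model. It names between-clinic and between-nurse variation as what the results are corrected for.

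**Baseline data.** Under Laboratory tests, "OGTT was taken at 8-12 and 26-28 weeks' gestation and 1 year postpartum". The other main GDM risk factors (BMI, age, obstetric history, diabetes in relatives) are inclusion criteria and so are established at entry.

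**The concern.** Randomising clusters protects the comparison of clusters. It protects the comparison of individuals only if entry to the study does not depend on the arm. Here a trial-clinic nurse invites a woman to added counseling and monthly group exercise, while a control-clinic nurse invites her to usual care plus measurements. Either the offer itself or the way it is made could attract women at different GDM risk. The direction cannot be predicted: volunteers for counseling might be more health-conscious, or might be those who already know that their risk is high.

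A random effect for clinic or nurse gives an appropriate standard error in the presence of clustering. It does not remove a systematic difference between the women in the two arms. If adjustment for individual risk stays optional, the primary contrast may carry that difference, and the choice of covariates stays open until the data are seen.

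**Working it through.** **Step 1. Order of events.** Allocation is by municipality, the recruiting nurses belong to trial or control clinics, consent is signed at the first visit, and that visit also holds the first counseling session in trial clinics. The article does not state in one place that allocation preceded recruitment or that nurses were unmasked, but these sections together imply both.

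**Step 2. The plan's own sample size.** Inputs from Power calculations and sample size: p0 = 0.40, p1 = 0.24, k = 0.1, m = 30 women per cluster, power 0.80, significance level 0.05 (taken as two-sided), dropout 25%.

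Pair-matched formula: c = 2 + (1.96 + 0.84)² × [W + B] / (p0 − p1)²
- W = 0.40×0.60/30 + 0.24×0.76/30 = 0.01408 (within clusters)
- B = 0.1² × (0.40² + 0.24²) = 0.002176 (between clusters)
- c = 6.98, so 7 per arm; 7 × 2 × 30 = 420; 420/0.75 = 560

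This reproduces the stated 560. Power at c = 7 is 0.80.

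**Step 3. How far an imbalance could move the result.** The document gives no imbalance and no strength of prediction, so both are assumed. Let logit(risk) = a + b·x, with x a standard normal baseline risk score and b = ln(OR per SD). Choose a so that the average risk is 40%, then shift the mean of x by 0.2 SD and average again.

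| OR per SD | a | Shift in risk | Share of 16 points |
|---|---|---|---|
| 2 | −0.449 | 3.0 points | 19% |
| 2.5 | −0.478 | 3.8 points | 24% |
| 3 | −0.505 | 4.3 points | 27% |

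Applying the odds ratio directly to a 40% risk, expit(logit 0.40 + 0.2·b) − 0.40, gives 3.4 to 5.4 points. That overstates the shift, because a per-SD odds ratio is conditional on the score and has to be averaged over women.

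**Step 4. Consequence for the test.** Assume no true effect and trial-arm women at lower baseline risk by d.
- Standard error over 7 pairs at d = 4 points: √{[0.40×0.60/30 + 0.36×0.64/30 + 0.01×(0.40² + 0.36²)]/7} = 0.0515.
- The two-sided rejection rate, nominally 5%, becomes 8.9% at d = 3 points and 12.1% at d = 4 (normal approximation), or 7.8% and 10.1% (paired t, 6 df).
- If instead the effect is as planned and the imbalance runs against it, power under the formula of Step 2 falls from 0.80 to 0.68 at 2 points and 0.54 at 4 points.

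**Step 5. What adjustment could gain in precision.** Replace W by W(1 − R²), where R² is the assumed share of within-cluster variance explained by baseline covariates. Power = Φ{0.16/√[(W(1 − R²) + B)/5] − 1.96}, where 5 = 7 − 2 as in Step 2.

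| R² | Standard error | Power |
|---|---|---|
| 0 | 0.0570 | 0.80 |
| 0.10 | 0.0545 | 0.84 |
| 0.20 | 0.0518 | 0.87 |

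**Step 6. Room for the covariates.** Expected GDM cases at the planned rates are 210×0.40 + 210×0.24 ≈ 134, enough for a short list of baseline terms.

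**The case against.** **The article is a condensed account, and covariate lists belong in the full plan.** This stands. A missing list would not be a finding by itself, and a reader might wrongly infer that the comparison is declared unadjusted. The Statistical analysis section does not say so, and it expressly leaves room for individual-level influences. What remains is narrower: given this recruitment design, the correction that the section does state is not the one needed, and the one needed is left optional.

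**Bias is not shown.** This also stands. A reader might infer that imbalance passes into the primary result as a matter of course. That would require an actual imbalance and a final model without individual risk factors, and the article establishes neither.

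**There are safeguards.** Eligibility criteria are the same in both arms. The baseline OGTT exclusion cuts off the upper end of an important predictor. Pairs are matched on estimated GDM incidence. Nurses log women invited and eligible. Consenting non-participants supply a baseline questionnaire and registry data. These reduce the risk or make it visible. However, glucose below the cut-offs, BMI, age and history can still differ by arm, municipal matching does not balance volunteers, and a log does not alter an estimate.

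**Adjustment is not a full remedy.** True: health-consciousness, for example, is only partly captured by the clinical risk factors.

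**Change scores.** A reader might take "Additional outcomes are changes in maternal physical activity" to mean that raw change scores will be analysed. The text does not support this. The wording names additional outcomes, not the secondary ones, and no change-score model is specified.

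**Conclusion.** The point holds as a risk that the plan could reduce at almost no cost, not as a demonstrated bias. Recruitment by clinic staff in already-allocated municipalities allows individual GDM risk to differ by arm, and correcting for clinic and nurse variation does not remove such a difference. Under assumed inputs (odds ratio 2 to 3 per SD, 0.2 SD imbalance) the distortion is about 3.0 to 4.3 points, in either direction, against a planned effect of 16. Under an assumed R² of 10 to 20%, adjustment would raise power from 0.80 to about 0.84 to 0.87. None of these assumed inputs comes from the article. The sample size of 560 is not in question.

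**What to change.** In the Statistical analysis section, or in the analysis plan before outcome data are examined:

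1. Make the primary multilevel model for GDM adjusted for named baseline covariates: OGTT fasting and 2-hour glucose at 8-12 weeks, pre-pregnancy BMI, age, earlier GDM or glucose intolerance or macrosomic newborn, and diabetes in relatives.
2. Report the unadjusted result beside it, both as risk differences, so that they can be compared with each other and with the 16-point design effect.
3. Use the existing log to tabulate invited, eligible and enrolled women by arm, with baseline risk factors where held.
4. State that adjustment removes only measured imbalance, and that recruitment by unmasked clinic nurses remains a limitation.

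The cost is wording and a little more modelling. The covariates are already collected, the sample size does not change, and the unadjusted result is still available.

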#### Exclusion criteria

Women were excluded if they had at least one of the following: a pathological value in the baseline oral glucose tolerance test (OGTT) at 8-12 weeks' gestation (blood glucose > 5.3 mmol/l at fasting, > 10.0 mmol/l at 1-hour or >8.6 mmol/l at 2-hour), pre-pregnant type 1 or 2 diabetes, inability to speak Finnish, age < 18 years, twin pregnancy, physical restriction preventing from physical activity, substance abuse, treatment or clinical history of psychiatric illness.

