### Power calculations and sample size

The randomization of maternity clinics as clusters instead of women as individuals was taken into account in the power calculations [66]. When planning the RCT, no published studies on prevention of GDM among women at risk or data on decrease in the incidence of GDM were available. The power calculations for pair-matched study were based on the assumption of detecting a 40% reduction of incidence of GDM from 40% in the control clinics to 24% in the trial clinics. The power of the study was 0.80, significance level 0.05 and coefficient of variation of rate between clusters, indicating cluster sampling, 0.1. The dropout rate during the study (estimated 25%) was taken into account in the sample size calculations. Thus, a total number of 560 women should be recruited to the study. The number of women in the end of the study would thus be 210 + 210 (7+7 clinics, 30 women/clinic).

Success in recruitment and proportion of drop-outs (25%) were estimated based on the pilot study [28,67]. Our recruitment target seemed feasible since the annual number of deliveries in Pirkanmaa region was approximately 5000 [31] and at least fourth of these women were estimated to fulfill the inclusion criteria of this study.

The sample available for the 1-year follow-up (n = 462) is adequate to discover 5-20% difference of metabolic syndrome in trial and control groups. Intracluster correlation coefficient in the current study is estimated as 0.12 (valid when 0.10-0.30) [68].

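### The enrolment minimum of 30 women per municipality equals the number needed after drop-out, so it does not by itself secure the stated power of 0.80

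*Protocol article*

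**What the plan says.** Two sections of the Protocol article set numbers for recruitment.

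- **Recruitment of study population** gives the only rule per municipality: "Recruitment was planned to continue until at least 30 women were enrolled in each municipality".
- **Power calculations and sample size** states the design assumptions: "detecting a 40% reduction of incidence of GDM from 40% in the control clinics to 24% in the trial clinics", and "The power of the study was 0.80, significance level 0.05 and coefficient of variation of rate between clusters, indicating cluster sampling, 0.1". On losses it says: "The dropout rate during the study (estimated 25%) was taken into account in the sample size calculations". It then gives the number to recruit, "Thus, a total number of 560 women should be recruited to the study", and the number expected to remain: "The number of women in the end of the study would thus be 210 + 210 (7+7 clinics, 30 women/clinic".

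Two other sections bear on the point. Statistical analysis says that information on drop-outs comes from the birth registry and that the intention-to-treat analyses follow that linkage. Outcome measurements defines GDM, for the primary outcome, by the oral glucose tolerance test at 26-28 weeks.

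**The concern.** The same number, 30, appears in two roles. In the power section it is the count per cluster that remains at the end of the study. In the recruitment section it is the count enrolled at which a municipality has met its minimum. The plan's own 25% loss lies between these two counts, and the recruitment rule makes no allowance for it.

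A trial in which every municipality meets its minimum can therefore fall well short of the sample on which the 0.80 rests. Cluster size matters here because the number of pairs is fixed at seven: women missing from one municipality cannot be made up by adding clusters. At stake is the stated power for GDM, a primary outcome.

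**Working it through.** **Inputs** (all from Power calculations and sample size unless noted)

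- Control incidence p0 = 0.40; intervention incidence p1 = 0.24; difference 0.16.
- Between-cluster coefficient of variation k = 0.1.
- Power 0.80, significance level 0.05. Sidedness is not stated; two-sided is assumed because it reproduces the plan's figure.
- Pair-matched design with 7 pairs. The unit randomized is the municipality (Study design, setting and group allocation), so the 7+7 clinics are read as 7+7 municipalities.
- Drop-out 25%.

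**Step 1: head counts**

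- Needed at the end: 14 × 30 = 420.
- To recruit: 420 / (1 − 0.25) = 560, which is 560 / 14 = 40 per municipality on average. This matches the plan.
- At the enrolment minimum: 14 × 30 = 420 enrolled, which is 560 − 420 = 140 short.
- Left from that minimum after 25% loss: 30 × 0.75 = 22.5 per cluster, or 315 in total.

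**Step 2: reproduce the plan's power**

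The usual formula for the number of pairs c in a pair-matched cluster trial of proportions (Hayes-Bennett), with n analysed per cluster, is

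c = 2 + (1.96 + 0.8416)² × V / (p0 − p1)²,

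V = [p0(1 − p0) + p1(1 − p1)] / n + k²(p0² + p1²).

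The two parts of V are (0.24 + 0.1824) / n = 0.4224 / n and 0.01 × (0.16 + 0.0576) = 0.002176.

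For n = 30: V = 0.01408 + 0.002176 = 0.016256, so c = 2 + 7.849 × 0.016256 / 0.0256 = 6.98, or 7 pairs. Power with 7 pairs is Φ(√[(7 − 2) × 0.0256 / V] − 1.96) = Φ(2.806 − 1.96) = 0.801. The stated design is recovered.

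**Step 3: the same formula at other numbers analysed, 7 pairs**

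| Situation | n per cluster | Pairs needed | Power |
|---|---|---|---|
| Plan: 40 enrolled, 25% lost | 30 | 6.98 | 0.80 |
| 30 enrolled, all drop-outs recovered | 30 | 6.98 | 0.80 |
| 30 enrolled, half of drop-outs recovered (assumption) | 26.25 | 7.60 | 0.75 |
| 30 enrolled, no drop-outs recovered | 22.5 | 8.42 | 0.70 |

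For n = 22.5: V = 0.018773 + 0.002176 = 0.020949, and power is Φ(2.472 − 1.96) = 0.696.

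**Step 4: dependence on the formula**

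A paired t-test with 6 degrees of freedom gives 0.789 at n = 30 and 0.685 at n = 22.5. The unmatched version (1 added in place of 2) gives 0.867 and 0.773; with no small-sample term the figures are 0.913 and 0.833. Only the pair-matched version reproduces 7 clusters per arm with 30 women each at 0.80, and it agrees with the section's wording: "The power calculations for pair-matched study were based on the assumption". Each version loses about 0.08 to 0.11 of power.

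**The case against.** There are four arguments on the other side.

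**The rule is a floor.** It says at least 30, and the power section separately sets 560 in total. Both can be met at once. For illustration (an assumption), seven municipalities enrolling 30 and seven enrolling 50 total 7 × 30 + 7 × 50 = 560. After 25% loss the cluster sizes are 22.5 and 37.5, with harmonic mean 2 / (1/22.5 + 1/37.5) = 28.1, and the formula gives power of about 0.78. This argument stands. A reader might infer that recruitment ends at 30, or that the two sections are irreconcilable; the documents support neither. What remains is that the only rule given per municipality permits closure at a number that does not protect the stated power.

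**Drop-outs may not be lost to analysis.** The plan links to the birth registry before the intention-to-treat analysis, and it uses the registry for GDM incidence among non-participants, so GDM status is held there. Newborn weight, the other part of the primary outcome, comes from hospital records or the maternity card. This stands in part. GDM is defined by a study glucose tolerance test at 26-28 weeks, and the article does not say that a registry diagnosis replaces it. The sample size itself treats drop-outs as lost, since it inflates 420 to 560.

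**The 462 women available at one year exceed 420.** This suggests that recruitment went beyond the minimum overall. It does not settle the matter: 462 is a total and not a count per cluster, and the recruitment section brings non-participants who completed the baseline questionnaire into the follow-up study.

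**Exclusions at the baseline glucose test.** A reader might infer a further loss, because consent is signed at the first visit while "a pathological value in the baseline oral glucose tolerance test (OGTT) at 8-12 weeks' gestation" is an exclusion. The article does not say that such women count towards the 30, and it gives no exclusion rate. No power figure for this loss can be supported.

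**Conclusion.** The point holds as a mismatch between the enrolment minimum and the sample size. The minimum of 30 enrolled equals the number needed after drop-out, whereas the plan's own total implies an average of 40. Meeting the minimum everywhere would therefore not secure the stated 0.80.

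Its size is conditional. Power is about 0.70 only if all 14 municipalities close at 30 and none of the 25% who drop out contributes a GDM outcome; half recovery gives about 0.75 and full recovery about 0.80. A reader might take 0.70 as the power of the trial. The documents do not support that, since they also require 560 in total and plan registry linkage. It is the lower end of what the enrolment rule allows under the plan's inputs. These figures rest on the stated incidences, the coefficient of variation of 0.1, seven pairs, and a two-sided 0.05 level, which is assumed.

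**What to change.** Reconcile the two sections.

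1. In Recruitment of study population, state the target as 560 women in total, an average of 40 enrolled per municipality, and say that 30 per municipality is the number expected after drop-out. A flat minimum of 40 in every municipality is not needed. It would be stricter than the plan's total, because any municipality above 40 would take the trial past 560, and it could be hard to reach in the smallest municipalities.
2. Recruitment is described in the past tense, so a reworded target cannot change it. Restate the power from the actual number of women analysed for GDM in each cluster, and give about 0.70 as the lower bound under the plan's inputs.
3. In that restatement, say how many drop-outs have a GDM outcome from the registry, since this moves the figure between about 0.70 and 0.80 when enrolment is at the minimum.

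The cost is a sentence or two and one recalculation. No woman beyond the planned 560 is asked for; the possible price is a less favourable stated power.
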